## ***Sample size***

The prevalences of severe anaemia at delivery and low birth weight have been shown to be about 12% and 5.7% respectively among Gambian multigravidae who received varying doses of SP-IPT (Mba*ye et a*l. 2006). In the absence of local data from the proposed study site, we estimate that the prevalences of severe anaemia in the third trimester and low birth weight will be 12% and 6% respectively in the LLIN +SP-IPTp arm of this study, similar to the Gambian population.

For trial planning we have set a non-inferiority margin of 5%. This means we would deem the LLIN + RDT screening with SP or AQ+AS treatment options to be inferior to the LLIN +SP-IPTp option if the prevalence of severe anaemia at 34 to 36 weeks is 5% greater in the LLIN+RDT with SP or AS+AQ treatment arm than that is observed in the LLIN+SP-IPT arm. Since we expect the prevalence of severe anaemia in the LLIN +SP-IPTp arm would be 12%, we need 887 women per arm to detect a 5% difference between the two study arms at 95% significance with 90% power. Considering a 20% dropout rate we need 1110 women per arm.

Setting a non-inferiority margin of 5% seems clinically and statistically relevant; and yields a sample size that makes the execution of the study feasible within the time frame and with the resources available. Choosing a smaller margin than 5%may be too tight requiring large sample size of over 2000 per arm which might not be feasible and achievable within the time frame; a larger margin than 5% may be too liberal to compare the public health impact of these interventions.

We estimate that 925 women per arm can show with 90% power at 95% significance level and accounting for a 20% dropout rate, that the prevalence of low birth weight associated with the LLIN + RDT screening with or without SP or AQ+AS treatment is no worse than LLIN + SP-IPTp by a margin of 4%.

Since, a sample size of 1110 per arm is adequate to detect any effects of the interventions on both birth weight and maternal Hb, a total of 3330 pregnant women will be recruited into this study.

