# BACKGROUND & RATIONALE

*Plasmodium falciparum* infection in pregnancy is associated with an increased risk of maternal and foetal complications including maternal anaemia and low birth weight (Brabin 1991; Menendez 1995). The pattern and severity of complications depend on gravidity, gestational age, age and HIV/AIDS and a woman’s pre-existing immunity, which is influenced by the local malaria transmission profile (WHO 2004). The WHO has recommended a package of interventions for preventing and controlling malaria infection in pregnancy in endemic areas which includes; the early diagnosis and treatment of malaria (EDT), intermittent preventive treatment during pregnancy (IPTp) using Sulphadoxine-Pyrimethamine (SP) and the use of insecticide treated bed nets (ITNs) (WHO 2004).

The policy of SP-IPTp for pregnant women has been shown to be efficacious, easy to administer, safe and tolerable (Pari*se et a*l. 1998; Verhoe*ff et a*l. 1998; Shulm*an et a*l. 1999; Rogers*on et a*l. 2000; van Ei*jk et a*l. 2004; Kayent*ao et a*l. 2005). Currently, SP-IPTp has been rated as having the most favourable effectiveness profile in terms of its low cost, compliance and reduced morbidity and mortality resulting from the prevention of maternal anaemia and low birth weight (Goodm*an et a*l. 2001; Newm*an et a*l. 2003). However, implementation of IPTp in most settings is limited by social, cultural, economic and operational challenges despite good coverage of antenatal services (Rogers*on et a*l. 2000; Hol*tz et a*l. 2004). In Ghana, implementation of SP-IPTp is currently being piloted in only 20 of its 110 districts (Dod*oo et a*l. 2005). The resistance to SP has been spreading across sub-Saharan Africa and thus the effectiveness of SP-IPTp has been questioned (Newm*an et a*l. 2003). There are very limited antimalarial drugs with plasma half life comparable to SP (e. g. Mefloquine) that could be used to replace SP for IPTp in areas with high SP resistance. Furthermore there is very limited data on the efficacy and safety during pregnancy of drugs with potentials to replace SP for IPTp. Thus evaluation of safety and efficacy of antimalarials drugs suitable for IPTp and alternative approaches to reduce the burden of malaria during pregnancy are needed urgently.

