## Study outcomes

Primary

- 1. Prevalence of severe maternal anaemia (Hb < 8g/dl) at 34 to 36 weeks of gestation.

Secondary

1. Prevalence of low birth weight (BW < 2500g) at delivery or within 72 hours of delivery.
2. Prevalence of maternal anaemia (Hb < 11g/dl) at 34 to 36 weeks of gestation.
3. Prevalence of placenta parasitaemia.
4. Incidence of post intervention malaria cases
5. Proportions of congenital anomalies in live births among the intervention groups stratified by gestation, gravidity, parity and age.
6. Proportions of spontaneous abortions, intrauterine death, stillbirths, neonatal and maternal mortality and pre-term deliveries.
7. Cost per severe maternal anaemia averted.
8. Cost per (non-severe) maternal anaemia averted.
9. Cost per peripheral malaria case averted.
10. Cost per placenta malaria averted.

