**Inclusion Criteria**

A pregnant woman will be eligible to be included in the study if: -

1. Her pregnancy is confirmed at 16 to 24 weeks at their first booking.
2. She is willing to participate and complete the test schedule, and has given informed consent.
3. She is willing to have supervised delivered at maternity units in the district.
4. She lives within the study district.

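### The 90% power rests on event rates from multigravidae although all gravidities are enrolled, and the sample size quoted against a tighter margin names no margin and is too high for margins between about 3.7 and 5 points.

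*Protocol*

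**What the plan says.** The protocol's Sample size section reports severe anaemia at delivery of about 12% and low birth weight of 5.7% "among Gambian multigravidae who received varying doses of SP-IPT". It explains the outside source by "In the absence of local data from the proposed study site" and then assumes that the rates "will be 12% and 6% respectively in the LLIN +SP-IPTp arm of this study, similar to the Gambian population". With a 5-point non-inferiority margin it arrives at 887 evaluable women per arm for 90% power, or 1110 after 20% dropout. For low birth weight, with a 4-point margin, it gives 925 per arm including dropout. It recruits 1110 per arm to serve both outcomes.

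The same section argues against a margin tighter than 5% as "requiring large sample size of over 2000 per arm". It does not say which margin, or whether dropout is included.

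Elsewhere the population is broader than the source. The gestational entry criterion is "Her pregnancy is confirmed at 16 to 24 weeks at their first booking", and neither the inclusion nor the exclusion list limits gravidity or parity. Background & Rationale states that "The pattern and severity of complications depend on gravidity", among other factors. Study outcomes asks for congenital anomalies to be reported "stratified by gestation, gravidity, parity and age", so a mix of gravidities is expected. The primary outcome is severe anaemia at 34 to 36 weeks, not at delivery.

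**The concern.** The protocol names gravidity as a driver of the complications it studies, then plans on a source that leaves out first pregnancies and calls the two populations similar without comment. With a fixed absolute margin, the variance of the risk difference depends on the control rate. If the rate in the enrolled mix is above 12%, the trial has less than the stated power. If it is below 12%, power is higher, but 5 points becomes a looser margin in relative terms: 5/12 = 42% of the control rate at 12%, and 5/10 = 50% at 10%.

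The sample size set against a tighter margin is part of the case for 5 points. If it is too high for margins just below 5%, a reader cannot tell which tighter margins were really out of reach.

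**Working it through.** **Inputs.** From Sample size: control rate p = 0.12, margin 0.05, 90% power, 20% dropout; for low birth weight, p = 0.06 and margin 0.04. From Study site and population: 220 + 80 = 300 registrations a month. From Enrolment Procedures: 18 months of recruitment. The stated 95% significance reproduces as one-sided 0.025. Control rates other than 12% and 6% are assumptions, since the documents give none.

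**The plan's own figures.** With a true difference of zero, n per arm = 2p(1−p)(1.96 + 1.2816)² / margin², where (1.96 + 1.2816)² ≈ 10.507.
- Severe anaemia: 0.2112 × 10.507 / 0.0025 = 887.7. The plan's 887 divided by 0.8 is 1109, against the stated 1110.
- Low birth weight: 0.1128 × 10.507 / 0.0016 = 741, and 741 / 0.8 = 927 after rounding up, against the stated 925.

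All three figures reproduce within rounding.

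**Power at other control rates.** Power = Φ(margin / √(2p(1−p)/n) − 1.96).

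Severe anaemia, margin 0.05, n = 887:

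| Control rate | Power |
|---|---|
| 10% | 94% |
| 12% | 90% |
| 15% | 84% |
| 17% | 80% |
| 20% | 75% |

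Worked line for 15%: √(2 × 0.15 × 0.85 / 887) = 0.01696; 0.05 / 0.01696 = 2.949; 2.949 − 1.96 = 0.989; Φ = 0.839.

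Low birth weight, margin 0.04, n = 1110 × 0.8 = 888: 94% at 6%, 87% at 8%, 80% at 10%.

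**What a mixed population might look like.** This is purely illustrative. Suppose 20% of women are primigravidae at 1.5 times the multigravid rate: 12% × (1 + 0.20 × 0.5) = 13.2%. Suppose 35% at twice the rate: 12% × (1 + 0.35) = 16.2%. Power is then 87.5% and 81.5%. To reach 20% at a twofold ratio, about 67% would have to be primigravidae (12% × 1.67 = 20%), so that row is an extreme.

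**Sample size by margin at p = 0.12.** Numerator 0.2112 × 10.507 ≈ 2.219.

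| Margin | Evaluable per arm | With 20% dropout |
|---|---|---|
| 5% (plan) | 887 | 1110 |
| 4.5% | 1096 | 1370 |
| 4% | 1387 | 1734 |
| 3.5% | 1812 | 2265 |
| 3% | 2466 | 3083 |

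The requirement passes 2000 evaluable at √(2.219/2000) = 3.3 points. It passes 2000 recruited (1600 evaluable) at √(2.219/1600) = 3.7 points.

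**Feasibility.** Registrations: 300 × 18 = 5400. A 5% margin takes 3330 (62%), 4.5% takes 3 × 1370 = 4110 (76%), and 4% takes 3 × 1734 = 5202 (96%), all before gestational limits, exclusions and consent.

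**The case against.** The protocol says openly that it has no local data, and its arithmetic is sound. The true rate may well be below 12%. Every arm gets nets and daily haematinics, women with haemoglobin below 5 g/dl are excluded, and the background cites net studies that found less anaemia. At 10% the power is 94%. This stands: the direction of the error cannot be settled from the documents, and any range must extend below 12%. It does not explain why the gravidity restriction of the source goes unremarked.

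On the margin, the protocol only says that a smaller one may need that many women, and it also rests the 5 points on clinical relevance and on resources. This stands too. A reader might infer that the figure of over 2000 is simply wrong. It is not: it is true at 3%, and at 3.5% once dropout is included. Nor does correcting it bring a 4% margin within reach, since 96% of expected registrations would have to be enrolled. A 4.5% margin is more arguable, and the protocol does not discuss it.

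A reader might also infer that low birth weight is seriously underpowered, by computing power from 925 × 0.8 = 740 evaluable women. The plan recruits 1110 per arm for both outcomes, so 888 is the right number. On the illustrative mix above (6.6% to 8.1%), power is then 92% to 87%.

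**Conclusion.** The point holds in a limited form. The 90% power for severe anaemia is conditional on a rate from a narrower population at a different time point, and the protocol does not show that this rate applies to the enrolled mix. The size depends on assumed rates: from 94% at 10% to 80% at 17%, with 75% at 20% only as an extreme. Low birth weight is the lesser concern because 888 evaluable women give 94% at the planned 6%.

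One might go further and call the trial underpowered or its margin untenable. The documents support neither. Multigravidae are eligible, the rate could lie on either side of 12%, and power stays above 80% across the illustrative mix. The sample-size argument against a tighter margin is unspecified, and it is too high for margins between about 3.7 and 5 points (with dropout). Correcting it does not overturn the 5-point choice on feasibility.

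**What to change.** 1. Keep 1110 women per arm. Justify the 12% and 6% control rates for a mixed-gravidity population measured at 34 to 36 weeks and at birth respectively, or re-estimate them. The earlier Ghanaian screening study in the background cannot supply the rate as cited, because the protocol reports only its relative reductions.
2. State power as a range that runs both ways. For severe anaemia at 887 evaluable: 94% at 10%, 90% at 12%, 84% at 15%, 80% at 17%, and 75% at 20% marked as an extreme. For low birth weight at 888 evaluable: 94% at 6%, 87% at about 8%, 80% at 10%.
3. Replace the blanket sample-size statement with the numbers by margin, evaluable and with dropout: 4.5% 1096/1370; 4% 1387/1734; 3.5% 1812/2265; 3% 2466/3083. Add the share of expected registrations that each would take, so that the feasibility argument is explicit.
4. Adjust the primary risk difference for baseline haemoglobin, which Enrolment Procedures already collects, to recover some precision. The gain cannot be quantified from the documents.

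The cost is a few lines of text and a less certain statement of power. No extra women and no new measurements are needed.

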A recent study of rapid diagnostic test (RDT) screening and treatment of parasitaemic pregnant women with amodiaquine (AQ) or SP singly or their combination in Ghana showed that this approach can reduce the prevalence of low birth weight by 30% and the prevalence of severe maternal anaemia (Hb < 8.0g/dl) at delivery by 45% (Tagb*or et a*l. 2006). These protective effects are similar to those obtained with SP-IPTp in Mali (Kayent*ao et a*l. 2005); Kenya (Pari*se et a*l. 1998; Shulm*an et a*l. 1999; Nja*gi et a*l. 2003) and Malawi (Verhoe*ff et a*l. 1997; Rogers*on et a*l. 2000). Although RDTs are not quantitative (Wongsrichanalai 2001) and peripheral parasite density in pregnancy may not correlate with placental parasitaemia, the use of OptiMAL® dipsticks to detect circulating parasite-specific lactate dehydrogenase (pLDH) may be of public health significance. The antenatal RDT screening was feasible and the cost was comparable to that of microscopy which costs an average of 10,000 and 15,000 cedis (1 US$=9100 cedis) in public and mission hospitals respectively.

The results of initial studies of the effects of ITNs on maternal anaemia and low birth weight were inconsistent because of the complexity of factors that determine acquisition and continued use of the nets. For example studies in Ghana (Brow*ne et a*l. 2001) and Kenya (Shulm*an et a*l. 1998) did not find any effect on malaria and anaemia in pregnancy following the use of insecticide impregnated bed nets; whilst other studies in the mesoendemic area of the Thai-Burmese border (Dol*an et a*l. 1993) and in The Gambia (D'Alessand*ro et a*l. 1996) found reductions in maternal anaemia and low birth weight with the use of ITNs.

However, a recent study of the impact of large scale use of ITNs among Kenyan pregnant women (ter Kui*le et a*l. 2003; ter Kui*le et a*l. 2003) showed significant reductions in malaria related adverse pregnancy outcomes. It is not clear though, how much extra benefit there is in combining use of ITNs and IPT during pregnancy (Nja*gi et a*l. 2003; Mba*ye et a*l. 2006).

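### The 4-point low birth weight margin is unjustified and, unless SP-IPTp cuts low birth weight by more than 40%, is at least as large as the whole SP-IPTp benefit

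*Protocol*

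**What the plan says.** Low birth weight is the first secondary objective and is framed as a demonstration that screening does no worse than SP-IPTp. In the protocol's Sample size section the planning rates are severe anaemia and "low birth weight will be 12% and 6% respectively in the LLIN +SP-IPTp arm of this study", borrowed from a trial in which severe anaemia and "low birth weight have been shown to be about 12% and 5.7% respectively among Gambian multigravidae". The birth-weight calculation reads "We estimate that 925 women per arm can show with 90% power at 95% significance level and accounting for a 20% dropout rate", the target being that screening "is no worse than LLIN + SP-IPTp by a margin of 4"%. The paragraph defending a margin concerns only the 5-point margin for severe anaemia, where anything smaller is described as "too tight requiring large sample size of over 2000 per arm". No rationale is offered for the 4 points. The section then concludes that 1110 women per arm suffices for both birth weight and maternal haemoglobin.

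The evidence on effect size is in Background & Rationale. A study of RDT screening and treatment in Ghana is said to show that "this approach can reduce the prevalence of low birth weight by 30"%. The text continues: "These protective effects are similar to those obtained with SP-IPTp in Mali", and adds Kenya and Malawi. On the setting of this trial, where every woman receives a net, it says: "It is not clear though, how much extra benefit there is in combining use of ITNs and IPT during pregnancy".

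**The concern.** A non-inferiority margin has to be smaller than the benefit of the active control. Otherwise a new strategy can forfeit all of that benefit and still sit inside the margin. Here the tolerated rise from 6% to 10% is a 67% relative increase (4/6), while the only effect size that the protocol offers for low birth weight is a 30% relative reduction. On a 6% base that is a small absolute benefit. At stake is what a positive birth-weight result would mean: it could be read as showing that screening preserves the protection of SP-IPTp when it is compatible with losing all of it. The 90% power quoted for this outcome is power for that weak claim only.

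**Working it through.** **Inputs.** From Sample size: 6% low birth weight and 12% severe anaemia on SP-IPTp; margins of 4 and 5 points; 90% power; 20% dropout; 1110 per arm, so 1110 × 0.8 = 888 evaluable. From Background & Rationale: a 30% reduction in low birth weight and a 45% reduction in severe anaemia from screening and treatment, with SP-IPTp described as similar.

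**1. Reproducing the plan's figures.** With equal true rates, one-sided 0.025 and 90% power, n = (1.960 + 1.282)² × 2p(1 − p)/margin², where (1.960 + 1.282)² ≈ 10.507.
- Low birth weight: 10.507 × 2 × 0.06 × 0.94/0.04² = 741 evaluable; 741/0.8 ≈ 926 enrolled (plan: 925).
- Severe anaemia: 10.507 × 2 × 0.12 × 0.88/0.05² = 888 evaluable; 888/0.8 = 1110 enrolled (plan: 887 and 1110).

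The stated sizes are arithmetically sound. The question is the margin.

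**2. Implied benefit of SP-IPTp.** The rate without it is 0.06/(1 − r), where r is the relative reduction.

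| r | Rate without SP-IPTp | Whole benefit (points) |
|---|---|---|
| 20% | 7.5% | 1.5 |
| 30% | 8.57% | 2.57 |
| 40% | 10.0% | 4.0 |
| 50% | 12.0% | 6.0 |

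At 30% the margin is 4/2.57 = 1.56 times the whole benefit. Starting from the source rate of 5.7% gives 0.057/0.70 − 0.057 = 2.44 points. The benefit exceeds 4 points only if r exceeds 40%.

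**3. Chance of a non-inferiority finding when the whole benefit is lost.** Φ((0.04 − d)/SE − 1.96), with d the true difference and unpooled SE at 888 per arm. At r = 30%, SE = √[(0.06 × 0.94 + 0.0857 × 0.9143)/888] = 0.01232, so Φ((0.04 − 0.0257)/0.01232 − 1.96) = Φ(−0.80) = 21%. At r = 20% it is 56%; at 40% it is 2.5%; at 50% it is below 0.1%.

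**4. Power at other margins.** Both arms at 6%, 888 evaluable: SE = √(2 × 0.06 × 0.94/888) = 0.01127 and power = Φ(margin/0.01127 − 1.96).
- 4 points: 94%
- 2.57 points (whole benefit at 30%): 63%
- 1.29 points (half of it): 21%

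The 95% CI half-width is 1.96 × 0.01127 = 2.2 points.

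**5. Smaller anaemia margins.** The formula in step 1 at 12%:

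| Margin (points) | Evaluable per arm | Enrolled per arm |
|---|---|---|
| 4.5 | 1,096 | 1,370 |
| 4.0 | 1,387 | 1,734 |
| 3.7 | about 1,621 | about 2,026 |
| 3.0 | 2,466 | about 3,082 |

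Enrolment passes 2000 per arm only at a margin of about 3.7 points or less.

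**The case against.** The strongest objection is that the 2.6-point benefit is a soft figure. The 30% comes from a study of screening and treatment, not of IPTp. Its comparator and confidence interval are not given, and it reaches SP-IPTp only through the word similar, spread over several studies, countries and outcomes. It is then applied to a rate from Gambian multigravidae. This stands, and it is why the benefit has to be given as a range. Above a 40% reduction the conclusion reverses. On the other side, every arm has nets, so the relevant benefit is that of SP-IPTp over LLIN alone, which the protocol itself calls unclear; it may be smaller than the table's 30% row.

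A reader might infer that a strategy with no effect would be accepted as non-inferior. The figures do not support that. At a 30% reduction its true difference lies inside the margin, but it would be declared non-inferior in about 21% of trials per comparison and fail in about 79%. Nor are the data uninformative. With equal arms at 6%, a half-width of 2.2 points would typically exclude a 2.6-point loss, whatever margin is named.

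A reader might also carry the criticism over to the primary margin. The protocol's figures do not bear that out: a 45% reduction ending at 12% implies 0.12/0.55 = 21.8% without treatment, a benefit of 9.8 points, of which a 5-point margin preserves about half.

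Finally, one might call the over-2000 statement simply wrong. The text names no smaller margin, and at 3 points the statement is true. It is too broad rather than false.

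**Conclusion.** The concern holds in conditional form. The 4-point margin is stated without justification and allows a 67% relative increase in low birth weight. For any SP-IPTp reduction below 40%, a strategy that loses the entire benefit lies inside it; at exactly 40% the two are equal. At the reduction of about 30% that the Background implies, the false-acceptance rate for such a strategy is about 21% per comparison, roughly eight times the nominal 2.5%, and there are two screening arms. This rests on the 6% planning rate, on transferring the 30% to SP-IPTp, on 888 evaluable women per arm and on a one-sided 0.025 test, the level that reproduces the plan's sizes. The outcome is secondary, and anaemia sets the enrolment. So the weakness limits what may be concluded about birth weight and does not undermine the trial's size or primary comparison.

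**What to change.** - Draw no non-inferiority conclusion for low birth weight from the 4-point margin. Report the risk difference with its 95% CI, and interpret it against the implied benefit range, stated openly as an assumption (about 2.6 points at a 30% reduction; 1.5 at 20%, 4.0 at 40%, 6.0 at 50%), noting that the benefit on top of nets may be smaller.
- Restate the power at 888 evaluable per arm: 94% at 4 points, about 63% at 2.6 and about 21% at 1.3. Qualify the sentence that treats 1110 per arm as sufficient for birth weight accordingly.
- Mean birth weight may be added as a supportive analysis, since midwives already record all birth weights. It should not replace the listed outcome: the protocol gives no standard deviation, margin or expected benefit in grams for it.
- Qualify the over-2000 statement for anaemia: about 1,370 enrolled per arm at 4.5 points, 1,734 at 4 points, and more than 2000 only at about 3.7 points or less.

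The cost is protocol wording and a less favourable stated power for a secondary outcome. No additional women or data are needed.
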